**Methods/design:**

In a randomized controlled trial, 90 primigravida women who attend for childbirth will be randomly assigned to one of three groups (intervention groups of either body acupressure or auricular acupressure; control, consisting of routine care). Computer-generated six-block randomization techniques will be used to determine the allocation sequence with a 1:1:1 ratio. To hide the allocation, the type of intervention will be written according to the generated sequence and put in opaque envelopes; these as well as questionnaires will be encoded. The pain score for all participants will be measured at the peak uterine contraction at 4-cm cervical dilation and at 10-cm dilation based on a visual analog scale (VAS). The duration of the active phase of labor in these groups will be recorded too. Data will be imported into SPSS-16 software. First, normality of the data distribution will be investigated. To compare labor duration among the research groups, ANOVA will be used, which will be followed, in case of significance, by the Scheffe post hoc test. Furthermore, Chi-squared test will be used to compare the categorized demographic variables and ANOVA or Kruskal–Wallis tests will be used to compare the quantitative variables in the studied groups. A significance level of 0.05 is considered significant.

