### Inclusion and exclusion criteria

#### Inclusion criteria

The inclusion criteria in the present study are primigravida women aged 19–35 years at gestational age of 37–42 weeks with a singleton pregnancy, cephalic presentation, no history of chronic diseases such as diabetes, cardiovascular disease, hypertension, hepatic and renal disorders, etc., a lack of pregnancy complications such as preeclampsia, gestational diabetes, bleeding, etc., a height above 150 cm, and admission at the beginning of the active phase (3–4 cm dilation).

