### Sample size estimation

To calculate the minimal clinically important difference (MCID) for the duration of the first stage of labor and the pain score, we used previous study data which examined the effect of auricular [24] and body [25] acupressure on labor pain intensity and labor duration. Using the method of Wyrwich et al. [26], MCID score for significant pain reduction during labor was one score based on visual analogue scale. Using the G*Power software 3.1.9.2, α = 0.05, and power = 0.80, considering SD = 1.4 and M0 = 7.2 for the labor pain score and 10% drop out of subjects, the sample size was calculated to be 30 patients for each group.

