### Data analysis

Once collected, the data are imported into SPSS-16 software. Firstly, normality of the data distribution will be investigated (via three methods, including Kolmogorov–Smirnov, histogram, and dispersion and central indices) and if the distribution of variables is not normal, then we will use an appropriate transformation. To compare the labor duration and pain score among the research groups, one way ANOVA test will be used, which will be followed, in case of significance, by Scheffe post hoc test. If there are potential confounding variables, a multiple linear regression test will be used. We will check for the assumptions and concerns of the regression model. Furthermore, Chi-squared test will be used to compare the categorized demographic variables in the studied groups. In order to compare the quantitative variables, in case of normal and abnormal distribution of the variables, ANOVA and Kruskal–Wallis tests will be used, respectively. The post hoc of these tests will be reported if needed. The study will be analyzed using an intention-to-treat (ITT) approach and using a multiple imputation strategy to account for missing outcomes in ITT. Also, apropos of the significance level, 0.05 is considered significant.

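### Significance tests of baseline characteristics between randomised arms cannot show whether the arms are balanced and should not choose covariates; describe baseline without p-values and fix a short covariate list in advance (minor)

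*Protocol article*

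**What the plan says.** Under Data analysis, the protocol article states that a "Chi-squared test will be used to compare the categorized demographic variables in the studied groups". Quantitative variables are to be compared by ANOVA or Kruskal–Wallis according to their distribution, with post hoc tests where needed. The Abstract has the same plan: "Chi-squared test will be used to compare the categorized demographic variables and ANOVA" or Kruskal–Wallis for the quantitative variables. The only significance level given is that "0.05 is considered significant".

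The same section compares pain score and labor duration by one-way ANOVA and then adds: "If there are potential confounding variables, a multiple linear regression test will be used". It names no covariate and gives no criterion for when one counts as a potential confounder.

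Under Randomization and blinding, the three arms come from a computer-generated sequence in a 1:1:1 ratio. Under Sample size estimation, "the sample size was calculated to be 30 patients for each group", which includes 10% dropout.

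**The concern.** When allocation is random, the arms are samples from one population for every characteristic that existed before allocation. The null hypothesis of a baseline test is then true by design. A p-value below 0.05 is a chance event, and a p-value above 0.05 reflects the small sample as much as it reflects balance. The report could call the arms different although randomisation worked, or comparable although a prognostic factor is visibly out of balance.

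A second consequence depends on a link that the text does not make. Adjustment is conditional, and the baseline comparisons are one obvious way for an analyst to settle that condition. If they are used in this way, covariates enter the model because of chance p-values and not because they predict pain or duration.

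**Working it through.** **Inputs from the protocol article.** 30 women per arm, "α = 0.05, and power = 0.80", a minimal important difference of 1 VAS point, SD 1.4 and 10% dropout (Sample size estimation); three arms; level 0.05 (Data analysis). With 10% dropout, 30 × 0.9 = 27 per arm remain, so both 27 and 30 are used.

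**Assumptions, not in the document.** The number of baseline variables (5 to 15, independent) and the correlation r between a covariate and the outcome (0.1 to 0.7).

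**The plan's own figure.** For a difference of 1 and SD 1.4, a one-sided 0.05 test of two groups needs 25 per arm, or 25 / 0.9 = 28 after dropout, close to the stated 30. A two-sided test needs 31 (32 with the t distribution), or 35 to 36 after dropout. This bears on the present point only in that 27 to 30 per arm is the right range to examine.

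**1. False alarms.** P(at least one p < 0.05) = 1 − 0.95^k.
- k = 5: 23%
- k = 10: 40%
- k = 15: 54%

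**2. How large an observed imbalance must be to be flagged.** If one arm differs from the other two by d SD, F = n(2/3)d²/2. Setting F to its 5% critical value on 2 and 87 degrees of freedom (3.10) with n = 30 gives d = √(2 × 3.10 / 20) = 0.56 SD. For a binary variable at 15/30 in two arms, the third arm must reach 24/30 before chi-squared is significant (p = 0.024).

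**3. How often imbalance occurs and is missed.** In simulated valid randomisations, the largest between-arm difference in a continuous covariate exceeds 0.5 SD in 13% (30 per arm) to 16% (27 per arm) of trials. ANOVA flags 39% and 31% of these, so 61% and 69% go unflagged. At 30 per arm, 90% of differences above 0.3 SD are missed and 81% above 0.4 SD.

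**4. Sensitivity to a systematic shift.** If one arm were truly shifted, the noncentrality is 30 × (2/3)d² and ANOVA power is 20% at 0.3 SD, 49% at 0.5 SD and 89% at 0.8 SD. The test is weak up to about 0.5 SD but not for large shifts.

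**5. Effect on an unadjusted contrast.** An imbalance of d SD moves the contrast by r × d × 1.4 VAS points. At d = 0.5 this is 0.21 (r = 0.3), 0.35 (r = 0.5) and 0.49 (r = 0.7), against a minimal important difference of 1.

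**6. Error rates if the tests did select the model.** Suppose the rule is to adjust only when the baseline p is below 0.05.
- In the 15% of trials with baseline p between 0.05 and 0.20, the unadjusted ANOVA has a false-positive rate of 6% to 10% for r = 0.3 to 0.6; the adjusted analysis holds about 5%.
- Over all trials, the type I error of the rule is about 4% to 5%.

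**7. Power, one arm 1 point lower, SD 1.4 (range over 27 to 30 per arm).**

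| r | Adjust only if baseline p < 0.05 | Always adjust |
|---|---|---|
| 0.3 | 77–81% | 80–84% |
| 0.5 | 77–82% | 87–91% |

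At r = 0.2 the gain from always adjusting is about 1 point; at r = 0.1 it is about zero.

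**The case against.** **No stated trigger.** A reader might infer that the baseline tests decide whether to adjust. The document does not say so. The regression sentence comes first, and the demographic tests follow as an additional analysis. Potential confounders could equally be chosen from prior knowledge. This stands, so everything about covariate selection is conditional.

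**No overall inflation.** A reader might also infer that the false-positive rate of the trial is raised. It is not. If the tests select nothing, the one-way ANOVA is unaffected; if they do select, the overall rate is still about 4% to 5%. The 6% to 10% applies only within a slice of trials.

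**Not every imbalance is missed.** The claim that the tests overlook most imbalances holds up to about 0.5 SD, not near 0.8 SD.

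**The power gain is not assured.** Nothing in the document shows that age, gestational age or height predicts labor pain, and eligibility already narrows their ranges. This stands.

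**Some tests may be legitimate.** The Abstract says "ANOVA or Kruskal–Wallis tests will be used to compare the quantitative variables in the studied groups", which is not limited to demographic variables. Under Assessments, the midwifery and demographic questionnaires are completed after the birth, so some items may arise after randomisation, and comparing arms on those is reasonable.

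**Detail left to a fuller document.** The exact covariate list might be found there. That does not answer the objection to the baseline tests, which the article positively plans.

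**Conclusion.** The point holds in limited form. The planned tests of pre-allocation characteristics answer no useful question. A significant result is a chance finding, with a 23% to 54% probability of at least one over an assumed 5 to 15 independent variables. A non-significant result leaves about 61% to 69% of imbalances above 0.5 SD unflagged.

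If, and only if, these tests also decide on adjustment, there are two further costs: conditional bias in trials with a missed imbalance in a prognostic covariate, and lost precision of about 3 power points at r = 0.3 and 9 to 10 at r = 0.5. Both depend on assumed correlations. Severity is minor: as written, no estimate or test of the pain or duration outcomes depends on the baseline p-values.

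**What to change.** In Data analysis and in the Abstract:

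1. For characteristics fixed before allocation, replace the chi-squared, ANOVA and Kruskal–Wallis comparisons with summaries by arm (n and %, mean and SD, or median and IQR) without p-values. Leave comparisons of any post-randomisation midwifery variables as they are.
2. State that no baseline p-value selects covariates.
3. Replace the conditional regression with pain and duration models that always include a short list fixed in advance from variables known before allocation. Candidates are maternal age, gestational age and height, which are already established for eligibility (for example "a height above 150 cm"). For pain at 10 cm, the 4-cm pain score is a natural addition if it is taken before the intervention starts, which the document should confirm.

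The cost is a few sentences and no new data. Each covariate uses one of the 90 − 3 = 87 residual degrees of freedom. If the covariates prove non-prognostic, there is no power gain and almost no loss.

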### Reporting of adverse events

Any kind of unwanted outcome in the participants will be reported.

### Patient and public involvement

Patients and the public were not directly involved in the development of this study protocol. However, the development of the research question and outcome measures is in accordance with previous published studies on patients’ priorities, experiences, and preferences. We will disseminate results to the study participants through journal publication as well as research conferences.

## Discussion

Improving the maternal and neonatal health is one of the sustainable development goals world-wide which Iran's Minestry of Health has strategic planning to reach this goal, too. Achieving these goals involves reducing the maternal and neonatal mortality rate due to complications of pregnancy and delivery, reducing the use of CS without indication and promoting normal delivery [42]. One way to promote natural childbirth is a painless labor. The American College of Obstetricians and Gynecologists has confirmed that the request for pain relief from the patient is indicative of the need for pain relief [43]. Labor pain relief methods are divided into non-pharmacological methods and pharmacological methods. Hypnosis, acupuncture, therapeutic touch, relaxation, massage therapy, and music therapy are non-pain relief methods [6]. Systemic medications, inhalation anesthesia, local anesthesia and general anesthesia are pharmacological methods of pain relief [43].

Based on available scientific resources, massage can reduce labor pain by the gate control mechanism of pain. In this way, massage activates large neural fibers and closes the gates of pain transfer. Another theory in this area is that massage may release endorphins and thereby reduce the pain [44]. In this study we will compare the effect of auricular acupressure and body acupressure on labor pain. In addition, we will study the effect of the two noted methods on duration of first stage labor.

### Trial status

Recruitment began in August 2018 and is ongoing. Data collection will probably be completed in December 2019.

## Data Availability

Original research data can be requested from the corresponding author. Additional files: Appendix 1: SPIRIT checklist.
